**b. Analyses, tables, and figures to be reported to SCORE by Gaining and Sustaining study researchers**

The following describes the tables and figures expected from SCORE studies, as well as approaches to analyzing the data and examples of SAS code.

**Table 1. Baseline characteristics of participants, by arm.**

This would include number of villages; number of participants; and age, sex, prevalence, and intensity assessed both by including all children and including only egg-positive children. Where appropriate, measures of dispersion should be included, for example, interquartile measures of intensity.

**Figure 1. Map of study villages, by arm.**

This can be presented as a single map, with different symbols for each of the arms, or as a series of maps.

**Table 2. Coverage and harms.**

Note that in Sm1 studies, only information on Arms 1-3 and treatment of SAC will be included.

|                     |              | SAC treated | SAC total | % SAC treated | Total population treated | Total population eligible for treatment | % total population treated |
|---------------------|--------------|--------------------|------------------|----------------------|---------------------------------|------------------------------------------------|-----------------------------------|
| Year 1       |              |                    |                  |                      |                                 |                                                |                                   |
|                     | Arm 1 |                    |                  |                      |                                 |                                                |                                   |
|                     | Arm 2 |                    |                  |                      |                                 |                                                |                                   |
|                     | Arm 3 |                    |                  |                      |                                 |                                                |                                   |
|                     | Arm 4 |                    |                  |                      |                                 |                                                |                                   |
|                     | Arm 5 |                    |                  |                      |                                 |                                                |                                   |
|                     | Arm 6 |                    |                  |                      |                                 |                                                |                                   |
| Year 2, etc. |              |                    |                  |                      |                                 |                                                |                                   |
|                     | Arm 1 |                    |                  |                      |                                 |                                                |                                   |

In addition to the table, information should be provided about

- How numerators and denominators were collected, by year if they changed over time
- Any particular issues or concerns related to MDA coverage
- A listing of the serious adverse events or harms

**Figure 2. Study flow by arm.**

The study flow diagram describes the process through the phases of a randomized trial. A sample study flow diagram and accompanying table are shown in Appendix I.

**Table 3. Descriptive results for baseline and Year 5.**

|                                                                                 | Arm 1
(cccc) | Arm 2
(ccss) | Arm 3
(cshh) | Arm 4
(ssss) | Arm 5
(sshh) | Arm 6
(shsh) |
|---------------------------------------------------------------------------------|------------------------|------------------------|------------------------|------------------------|------------------------|------------------------|
| No. tested at baseline                                                   |                        |                        |                        |                        |                        |                        |
| No. infected at baseline                                                 |                        |                        |                        |                        |                        |                        |
| Prevalence at baseline                                                   |                        |                        |                        |                        |                        |                        |
| No. tested at Year 5                                                     |                        |                        |                        |                        |                        |                        |
| No. infected at Year 5                                                   |                        |                        |                        |                        |                        |                        |
| Prevalence at Year 5                                                     |                        |                        |                        |                        |                        |                        |
| Absolute difference between prevalence at Year 5 and baseline            |                        |                        |                        |                        |                        |                        |
| Relative difference between prevalence at Year 5 and baseline (% change) |                        |                        |                        |                        |                        |                        |
| Village-level arithmetic mean* infection intensity at baseline           |                        |                        |                        |                        |                        |                        |
| Village-level arithmetic mean* infection intensity at Year 5             |                        |                        |                        |                        |                        |                        |
| Egg reduction rate (1-Year 5 intensity/baseline)                         |                        |                        |                        |                        |                        |                        |
| Individual-level arithmetic mean infection intensity at baseline*        |                        |                        |                        |                        |                        |                        |
| Individual-level arithmetic mean infection intensity at Year 5*          |                        |                        |                        |                        |                        |                        |

\*Taken as the mean of all per village means per arm, not the mean of all individuals in the arm

**Figure 3. Intensity categories, by Arm, by Year.**

This is a stacked bar chart, showing low, medium, and high intensity infections, by Arm, for Years 1-5.

Intensity categories are defined as:

- Sm: Low=1-99 epg, Medium=100-399 epg, high $\geq$ 400 epg
- Sh: Low 1-50 eggs/10 ml, high $\geq$ 51 eggs/10 ml

A supplemental table including the numbers used to make the chart should be available should modelers or other analysts want to use the exact data.

**Table 4. Comparisons of prevalence and intensity at Year 5 among arms.**

This table describes the primary outcomes.

|                       | Unadjusted prevalence model estimate (CI) | Adjusted prevalence model estimate (CI) | Unadjusted intensity ratio (CI) | Adjusted intensity ratio (CI) |
|-----------------------|--------------------------------------------------|------------------------------------------------|----------------------------------------|--------------------------------------|
| Arm 1 v. Arm 4 |                                                  |                                                |                                        |                                      |
| Arm 1 v. Arm 2 |                                                  |                                                |                                        |                                      |
| Arm 1 v. Arm 3 |                                                  |                                                |                                        |                                      |

|                |  |  |  |  |
|----------------|--|--|--|--|
| Arm 4 v. Arm 5 |  |  |  |  |
| Arm 4 v. Arm 6 |  |  |  |  |

*General approach to analysis:* The general approach is to use GEEs to estimate differences between the arms in year 5 only. We will report unadjusted estimates – with just village and arm fitted in the model – and adjusted estimates – where sex and age are also included in the model, along with weighting for number of children who provided data, because not all villages were able to sample 100 9-12 year old children.

ICC will be calculated using mixed models consistent with the GEE setup in the primary analysis.

All models will be based on individual level data on 9-12 year old children only.

*Sample code:* The following codes are provided as examples. Different studies may require further modification of the code below or may require different approaches.

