3. *Determine eligibility.* Determine eligibility of communities/villages by testing 50 school children in classes that include those ages 13-14. Each Study 1 will require a total of 75 villages (25 per study arm), and each Study 2 will require 150 villages (25 per study arm). Children who test positive in this initial survey should be treated. This will involve examining a mid-day urine in Sh villages, using either dipsticks or 2 filtrations of 10 ml each. In Sm villages this will involve testing a single stool, examining 2 slides per stool.

4. *Randomize.* After an adequate number of eligible communities/villages are identified, they will need to be randomly assigned to the arms of the study – 3 arms for a Study 1 and 6 arms for a Study 2. Regardless of the outcome of randomization, for example, an uneven distribution of a particular factor, villages may not be re-randomized.

[figure not shown]

[figure not shown]

There will be no stratification for randomization of Sh1 and Sm1 communities/villages. Sh2 and Sm2 communities/villages will be randomized with stratification by prevalence on initial screening using Proc Plan, according to an agreed-to protocol.

5. *Identify villages for layered studies (Sh2 and Sm2 only).* Layered studies include subtle morbidity, snail, and parasite genetics evaluations. Investigators funded under this RFP who are conducting Sh2 and Sm2 studies will also be funded to conduct subtle morbidity studies. Investigators funded under this RFP should participate with investigators conducting snail and schistosome population genetics studies to ensure snail collection and plans for parasite collection are in place before MDA.

6. *Sensitize communities.* A greater level of effort will be required to engage eligible communities in the full, multi-year study than was required for the initial eligibility survey. A simple standard approach will be developed to capture what activities are conducted to achieve sensitization.

7. *Train workers.* This includes training on data collection, drug delivery, reporting of adverse events, etc. Incentives may be paid in accordance with local practices and practices of non-government organizations in the area.

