### a. Overview of SCORE Gaining and Sustaining studies

The SCORE Gaining and Sustaining study protocol described the four types of studies to be conducted:

1. **Study Sm1:** Study 1 for *S. mansoni* was a cluster-randomized trial that compared MDA delivery strategies in study communities/villages with prevalence during eligibility testing of 10-24% by Kato-Katz stool examination.
2. **Study Sm2:** Study 2 for *S. mansoni* was a cluster-randomized trial that compared MDA delivery strategies in study communities/villages with prevalence during eligibility testing of  $\geq 25\%$  by stool examination.

3. **Study Sh1:** Study 1 for *S. haematobium* was a cluster-randomized trial that compared MDA delivery strategies in study communities/villages with prevalence during eligibility testing of 10-24% by urine filtration (or 5-20% by urine dipstick test for hematuria).
4. **Study Sh2:** Study 2 for *S. haematobium* was a cluster-randomized trial that compared approaches in study areas with prevalence during eligibility testing of  $\geq 25\%$  by filtration or  $\geq 21\%$  by dipstick.

For purposes of this protocol, a study community or village was required to have a primary school, because several arms of the study are school-based and every participating community must be eligible to be randomized to any of the study arms. However, a study community could have more than one school. If two nearby communities had schools with fewer than 100 children per school, but they were similar, they could be combined for purposes of this study and be considered as one study community. Two nearby communities that shared water sources and/or whose schools had overlapping catchment areas were not to be considered two villages for purposes of this study; one of the two could be chosen.

Prior to enrollment, village eligibility was determined by testing fifty 13-14 year-old children in each village. Once a village was enrolled in the study, the **primary outcomes of interest are prevalence and intensity among 9-12 year-old children**. A simple randomization procedure was used, without stratification. Re-randomization based on the first randomization results was not permitted.

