#### Unadjusted prevalence

The evaluation of unadjusted prevalence uses a binomial GEE with logit link function. Village\_ID is treated as the repeated subject, and we assume compound symmetry within a village. 'Lsmestimate' is used to test the pre-specified differences between arms.

```
ods trace off;
proc genmod data=allyears descending;
  where Study_Year = 5;
  class Study_Arm Village_ID / param=glm;
  model Sh = Study_Arm / dist=bin link=logit ;
  repeated subject=Village_ID / type=cs;
  lsmeans Study_Arm / cl;
  lsestimate Study_Arm "arm 2 vs. arm 1" -1 1 0 0 0 0 / cl;
  lsestimate Study_Arm "arm 3 vs. arm 1" -1 0 1 0 0 0 / cl;
  lsestimate Study_Arm "arm 4 vs. arm 1" -1 0 0 1 0 0 / cl;
  lsestimate Study_Arm "arm 5 vs. arm 1" -1 0 0 0 1 0 / cl;
  lsestimate Study_Arm "arm 6 vs. arm 1" -1 0 0 0 0 1 / cl;

  lsestimate Study_Arm "arm 3 vs. arm 2" 0 -1 1 0 0 0 / cl;
  lsestimate Study_Arm "arm 4 vs. arm 2" 0 -1 0 1 0 0 / cl;
  lsestimate Study_Arm "arm 5 vs. arm 2" 0 -1 0 0 1 0 / cl;
  lsestimate Study_Arm "arm 6 vs. arm 2" 0 -1 0 0 0 1 / cl;

  lsestimate Study_Arm "arm 4 vs. arm 3" 0 0 -1 1 0 0 / cl;
  lsestimate Study_Arm "arm 5 vs. arm 3" 0 0 -1 0 1 0 / cl;
  lsestimate Study_Arm "arm 6 vs. arm 3" 0 0 -1 0 0 1 / cl;

  lsestimate Study_Arm "arm 5 vs. arm 4" 0 0 0 -1 1 0 / cl;
  lsestimate Study_Arm "arm 6 vs. arm 4" 0 0 0 -1 0 1 / cl;

  lsestimate Study_Arm "arm 6 vs. arm 5" 0 0 0 0 -1 1 / cl;
estimate "O.R. arm 2 vs. arm 1" Study_Arm -1 1 0 0 0 0 / exp cl;
run;
```

Adjusted prevalence

The code is the same as for unadjusted prevalence, but with age, sex, and a weighting for village size added to the model.

villweight of individual = 1/# samples collected in village

```
ods trace off;
proc genmod data=allyears descending;
  where Study_Year = 5;
  class Study_Arm Village_ID Sex Age / param=glm;
  model Sh = Study_Arm Sex Age / dist=bin link=logit ;
  repeated subject=Village_ID / type=cs;
  weight villweight ;
  lsmeans Study_Arm / cl;
run;
```

ICC of prevalence

```
/*macro*/
%macro icc_bin(data, cluster, outcome, out, m, stval=%str(), pred=%str());
proc nlmixed data=&data.;
  parms b0=0 &stval. var1=1;
  eta = exp(b0 + &pred. r);
  pred = eta / (1+eta);
  model &outcome. ~ binary(pred);
  random r ~ normal(0,var1) subject=&cluster.;
  estimate 'ICC' var1/(var1 + (constant('PI')**2)/3);
  estimate 'Deff' 1 + (&m.-1) * (var1/(var1 + (constant('PI')**2)/3));
  ods output AdditionalEstimates=&out.;
run;

data &out.;
  set &out.;

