  cluster="&cluster.";
  outcome="&outcome.";
  m=&m.;
run;
%mend;
```

```
%icc_bin(sac, HHID, asc, hhl, 2.91, stval=%str(), pred=%str());
```

Unadjusted intensity

The code is the same as for unadjusted prevalence, but the distribution and link are changed.

```
ods trace off;
proc genmod data=allyears descending;
  where Study_Year = 5;
  class Study_Arm Village_ID / param=glm;
  model Sh = Study_Arm / dist=nb link=log ;
  repeated subject=Village_ID / type=cs;
  lsmeans Study_Arm / cl;
run;
```

Adjusted intensity

The code is the same as for the adjusted prevalence, but the distribution and link are changed.

```
ods trace off;
proc genmod data=allyears descending;
  where Study_Year = 5;
  class Study_Arm Village_ID Sex Age / param=glm;
  model Sh = Study_Arm Sex Age / dist=nb link=log ;
  repeated subject=Village_ID / type=cs;
  weight villweight ;
  lsmeans Study_Arm / cl;
run;
```

Figure 4. Village-level mean intensity by year, by arm.

Provide a line graph showing arithmetic mean intensity, by Year, by Arm.

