| (CI)                          |  |  |  |  |  |  |
| Mean hemoglobin in gm/dL (SD) |  |  |  |  |  |  |
| Prevalence of anemia % (CI)   |  |  |  |  |  |  |
| Mean Vo2 max score (SD)       |  |  |  |  |  |  |
| Mean PedsQL score (SD)        |  |  |  |  |  |  |
| Total Score                   |  |  |  |  |  |  |
| Physical                      |  |  |  |  |  |  |
| Emotional                     |  |  |  |  |  |  |
| Social                        |  |  |  |  |  |  |
| School                        |  |  |  |  |  |  |
| Liver pattern                 |  |  |  |  |  |  |
| B % (CI)                      |  |  |  |  |  |  |
| C or higher % (CI)            |  |  |  |  |  |  |

Tables 4 (multiple tables). Comparison between Arm 1 and Arm 6 of Year 5 morbidity outcomes.

For each outcome, the following type of table should be developed. The results should be as indicated in the cells below.

Example: Table 4A. Unadjusted and adjusted models for **anemia** at Year 5.

|                     | Unadjusted                   | Adjusted                   |
|---------------------|------------------------------|----------------------------|
| Arm (1 vs 6) | Parameter of Interest** (CI) | Parameter of Interest (CI) |
| Age          | ---                          | Parameter of Interest (CI) |
| Sex          | ---                          | Parameter of Interest (CI) |

*General approach to analysis:* For binary outcomes such as anemia status, the parameter of interest is typically the measure of association, such as odds ratio or relative risk. For models with other types of outcome, the parameter is the beta coefficient estimator from the corresponding models.

Generalized linear mixed effects models will be used to analyze the year 5 outcome. A generalized linear mixed effects model was chosen to account for random effects at the village level in year 5 comparison. The unadjusted model is a between-arm comparison without adjustment for other covariates. The adjusted model proposed here only includes adjustment for age and sex.

Generalized mixed effects models with normal, binomial, and multinomial distributional assumptions will be applied to address outcomes that are continuous, dichotomous, or categorical, respectively. SAS code examples for unadjusted models are provided below:

Sample code:

Linear mixed effects model code example

```
proc mixed;
  where Study_Year=5;
  class Person_ID Village_ID Study_Arm;
  model y = Study_Arm / solution;

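### The SAP Table 4 models leave out each village's Year 1 prevalence or intensity; this leaves chance imbalance uncorrected and loses precision by an amount the documents do not fix

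*Combined protocol and SAP*

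**What the plan says.** The main SAP, VI.b, Table 4, sets out the approach: "The general approach is to use GEEs to estimate differences between the arms in year 5 only". The unadjusted model is described as "with just village and arm fitted in the model". The adjusted model is the one "where sex and age are also included in the model, along with weighting for number of children who provided data". The sample code agrees: "model Sh = Study_Arm Sex Age / dist=bin link=logit" for prevalence and "model Sh = Study_Arm Sex Age / dist=nb link=log" for intensity, each with village as the cluster and a village weight. Supplemental Tables S1-S5 describe their estimates as adjusted for clustering, age and sex, and nothing else.

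Year 1 values in the same age group should exist for every village. Protocol step 11 and SAP II.c place a survey of 9-12-year-olds before MDA, and every arm sequence in SAP I begins with a treatment year, so no village started on a holiday. In the plan these values appear only in descriptive displays (Tables 1 and 3, Figures 3 and 4).

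On allocation the documents disagree. Protocol step 4 says "Sh2 and Sm2 communities/villages will be randomized with stratification by prevalence on initial screening using Proc Plan" and rules out stratification for Sh1 and Sm1. SAP II.a says "A simple randomization procedure was used, without stratification". No model contains a screening-prevalence term.

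For the cohort Year 5 comparison (SAP VII.b, Tables 4), "The adjusted model proposed here only includes adjustment for age and sex". Tables 5 model Year 1 and later values jointly, with an arm-by-year term.

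**The concern.** In a trial with a nominal 25 villages per arm and about 100 children per village, nearly all the uncertainty in an arm contrast comes from differences between villages. Age and sex are individual factors within a narrow age band and can explain little of that. The village's own starting level is the obvious candidate, and it has already been measured.

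The protocol forbids re-randomising after an uneven draw, so covariate adjustment is the main remaining way to deal with chance imbalance in starting prevalence. The Niger SAP (II.a) shows how much weight the programme gives to comparable starting levels: it says that when they differed markedly, valid comparisons could not be made. The cause there was faulty randomisation, but any comparison that uses Year 5 alone depends on starting level in the same way.

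At stake is the width of intervals that are often wide already, together with an uncorrected imbalance of unknown size in each country.

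**Working it through.** **1. Inputs.** From SAP II.c: 25 villages per arm and 100 children per village. From Supplemental Tables S1-S3, the first-priority contrast (SSSS vs CCCC) as a prevalence ratio: Kenya 0.73 (0.42, 1.28), Tanzania 1.09 (0.55, 2.16), Mozambique 1.01 (0.62, 1.69). Not in the documents, so assumed: ICC 0.1-0.3; r, the correlation of a village's Year 1 value with the village-level part of its Year 5 value, 0 to 0.7; intervals at 95%.

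**2. Reproducing stated figures.** 25 x 6 = 150 villages and 150 x 100 = 15,000 children, as SAP II.c says. The text supplied gives no power calculation to reproduce. For the reported intervals, SE = ln(U/L)/(2 x 1.96):
- Kenya SSSS vs CCCC: ln(1.28/0.42)/3.92 = 0.284, p = 0.27 (stated 0.28).
- Kenya SHSH vs SSSS, 1.68 (1.01, 2.80): SE 0.260, p = 0.046 (stated 0.045).

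These agree within rounding.

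**3. Share of variance a village baseline can reach.** s = ICC/(ICC + (1-ICC)/100). At ICC 0.1, s = 0.1/0.109 = 0.917; at ICC 0.3, s = 0.3/0.307 = 0.977.

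**4. Gain.** SE ratio = sqrt(1 - r²s); equivalent villages per arm = 25/(1 - r²s).

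| r (assumed) | SE ratio, ICC 0.1 to 0.3 | Fall in SE | Equivalent villages per arm | Simulated SE ratio |
|---|---|---|---|---|
| 0 | 1.00 | 0% | 25 | 1.01 |
| 0.3 | 0.958 to 0.955 | 4-5% | about 27 | 0.96 |
| 0.5 | 0.878 to 0.869 | 12-13% | 32-33 | 0.90 |
| 0.7 | 0.742 to 0.722 | 26-28% | 45-48 | 0.78 |

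The simulation used 2 arms x 25 villages x 100 children, a log link, robust standard errors and assumed variances. Type I error was 4-5%. It shows the linear formula to be slightly optimistic at r = 0.5 and 0.7.

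**5. What this would mean for reported contrasts.** Point estimates are held fixed and s is set to 1, the most favourable case. Kenya SSSS vs CCCC becomes (0.43, 1.24), (0.45, 1.18) and (0.49, 1.09) at r = 0.3, 0.5 and 0.7, so it spans 1 throughout. Kenya SSHH vs SSSS, reported as 1.49 (0.89, 2.49), becomes (0.91, 2.43), (0.95, 2.33) and (1.03, 2.15). These are illustrations only, because real adjustment would also move the estimates.

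**6. Hints in the documents.**
- Table S6 (redesigned Niger trial) gives Year 1 and Year 5 prevalence for ten subgroups. They correlate at 0.88, or 0.73 within Groups B and C. These are subgroup averages from another trial and cannot stand in for a village-level r.
- In Niger Group C, randomised by community, baseline was 480/3,357 = 14.3% (once yearly) vs 834/3,562 = 23.4% (twice yearly). Year 5 was 425/3,689 = 11.5% vs 392/3,724 = 10.5%. The Year 5 ratio is 0.91, the baseline ratio 1.64, and 0.91/1.64 = 0.56. This shows that imbalance can matter; it does not measure it in the four main-SAP countries.

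**The case against.** The strongest reply is that this is about efficiency, not validity. Randomisation protects the contrast, and the interval already allows for chance imbalance. That stands, and a reader who infers that the Year 5 estimates are biased by this omission goes beyond the documents. The six re-assigned Mozambique villages, analysed as treated (SAP II.c), are a separate matter.

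The SAP also calls itself a minimum analysis and allows the code to be modified. This is true, but permission is not prespecification: no baseline-adjusted analysis is named.

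Four further readings are tempting and not supported:
- **That the gain is known to be large.** r and the ICC are both assumed, and a gain of zero cannot be excluded. The 10-24% entry band may lower r in Sm1.
- **That the intervals cannot separate strategies.** Some prespecified contrasts were separated: Kenya SHSH vs SSSS 1.68 (1.01, 2.80), Mozambique SSHH vs SSSS 1.73 (1.08, 2.77), and Mozambique CCHH vs CCCC on intensity 2.15 (1.10, 4.18). The first-priority Kenya contrast spans 1 even at r = 0.7 in the illustration.
- **That a design stratum was wrongly dropped.** The protocol describes a plan for Sh2/Sm2 only, and the SAP says no stratification took place. If the stratum was used, leaving it out tends to make standard errors conservative.
- **That the cohort analysis ignores baseline.** Change from baseline is a primary cohort question (SAP VII.a, 1b) and Tables 5 address it.

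Two technical objections also stand. With the logit link, adding a prognostic covariate changes the odds ratio being estimated, so the formula does not carry over directly. And Kenya Year 1 egg counts were truncated at 42 per slide (SAP VIII), which makes raw Year 1 intensity a poor covariate there.

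**Conclusion.** The omission is confirmed in the SAP text, the sample code and the reported tables. It leaves chance baseline imbalance uncorrected and gives up precision to the extent that village values persist from Year 1 to Year 5. The fall in standard error forgone runs from nothing (r = 0) to 26-28% (r = 0.7) by the linear approximation, or 22% in simulation at r = 0.7. This assumes an ICC of 0.1-0.3 and 100 children per village. The documents do not locate the trials within that range.

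This is a worthwhile improvement from data already in hand. It is not evidence that the reported contrasts are invalid or that their conclusions would change. The conflict over stratification needs resolving whatever r turns out to be.

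**What to change.** In the adjusted Table 4 models of the main SAP:
- Add village Year 1 prevalence among 9-12-year-olds to the prevalence model.
- Add a transformed or categorised village Year 1 intensity to the intensity model, with a stated rule for villages whose mean is zero. For Kenya use Year 1 prevalence or categorised intensity, because of the truncation.
- State whether the effect is a prevalence ratio or an odds ratio. The code uses a logit link, while Tables S1-S5 report prevalence ratios.
- Reconcile protocol step 4 with SAP II.a against the allocation list, and include the screening-prevalence stratum for Sh2/Sm2 only if it was used. With Year 1 prevalence in the model it should add little.
- Keep the present models alongside, and label any re-analysis of the existing Year 5 data as post hoc.

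Adding the child's own baseline value to cohort Tables 4 is optional.

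The cost is SAP wording, one or two covariates already collected, a check of the allocation list and a re-run of the models. No new data collection is needed.
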